### Assessments

2.8

#### Primary outcome

2.8.1

The primary outcome for the trial is psychiatric inpatient readmission (of any type, voluntary or compulsory, as recorded by site) in the 12 months post discharge from the index admission (T2).

#### Secondary outcomes

2.8.2

Selection of secondary outcomes was guided by the change model for peer support in mental health services previously developed by the research team.^[27]^ Outcomes are collected as indicated below:

Strength of Social Network as measured using the Social Contacts Assessment,^[45]^ designed to collect data on both the frequency and quality of a range of types of social contacts in the preceding week, at end of intervention, 4 months post discharge from the index admission. (T1)Subjective quality of life as measured using the Manchester Short Assessment of Quality of Life,^[46]^ a well-validated patient-reported measure of quality of life, widely used in mental health studies, that has been shown to be sensitive to change. (T0, T1)Social inclusion as measured using the Social Outcomes Index (SIX),^[47]^ designed as an objective measure of social inclusion that can be easily extracted from items included in the Manchester Short Assessment of Quality of Life^[46]^ and an additional structured question about friendships. (T0, T1)Hope for the future, as measured using the Herth Hope Index,^[48]^ a self-report measure originally developed for use with older adults with chronic conditions and now increasingly used for adult mental health studies. (T0, T1)Severity of psychiatric symptoms, as measured using the Brief Psychiatric Rating Scale,^[49]^ a well-validated and widely used measure of clinical severity and the most frequently used severity measure in peer support trials to date. (T0, T1)Total number of psychiatric inpatient admissions (any type, voluntary or compulsory, as recorded by site). (T0, T2)Time to (first) readmission measured in days post discharge from index admission. (T2)Type of psychiatric admission (voluntary or compulsory, as recorded by site) for first readmission. (T2)Days in hospital (for all psychiatric admissions). (T0, T2)Use of accident and emergency (A&E) for psychiatric emergency measured as number of episodes of liaison psychiatry contact in hospital A&E. (T0, T2)Number of contacts with Crisis Resolution & Home Treatment Team. (T0, T2)Serious adverse events (SAE), as recorded in the SAE CRF (see below). (T2)

#### Health economic outcomes

2.8.3

Outcomes are collected as indicated below:

Quality-adjusted life years, calculated using EQ5D-5L,^[50]^ as widely applied in health economic evaluations of healthcare interventions. (T0, T1)Number of contacts and type of professional for community mental health team and mental health crisis services not otherwise listed under secondary outcomes above. (T0, T2)Number and type of contacts with non-NHS mental health services, as measured using a modified version of the Adult Service Use Schedule. (T0, T1)^[51]^Number, length, and type of contact with peer workers, measured using a structured online questionnaire.Number, length, and type of non-participant contact activities (e.g., supervision, training, office-based tasks) undertaken by peer workers and PWCs in delivering the intervention, measured using a structured online questionnaire.

#### Process measures

2.8.4

Measures of intervention process were informed by the peer support change model referred to above,^[27]^ and were collected as follows:

Strength of therapeutic relationship between participant and a) mental health professional with whom the participant has most contact, measured from the participant's perspective using the STAR Patient version and b) peer worker, measured from the participant's perspective, about the peer worker, using the STAR Patient version and from the peer worker's perspective, about the participant, using the STAR Clinician version.^[52]^ (T1)Experience of stigma within mental health services, as measured using the stigma subscale of the Barriers to Care Evaluation (BACE-3) Stigma Subscale.^[53]^ (T0, T1)Internalized stigma, as measured using the Questionnaire on Anticipated Discrimination (QUAD).^[54]^ (T0, T1)Other peer support received, measured using a set of structured questions. (T0, T1)Number, length, and type of contact with peer workers, as measured for the health economic evaluation above.Socio-demographic data are also collected at T0.

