### Aim

2.1

The aim of this study is to establish whether a peer worker intervention to support discharge from inpatient to community psychiatric care reduces psychiatric readmission in the 12 months following discharge, compared to CAU. Participants in the intervention group receive CAU, a Discharge Information Pack, and the peer worker intervention. Participants in the control group receive CAU and the Discharge Information Pack.

We also aim to:

establish whether the peer worker intervention is cost effective compared to the control condition;measure the impact of the peer worker intervention on a range of secondary intra-personal, behavioral, and service use outcomes;explore how the processes of intervention delivery relate to outcome.

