### Data collection methods

2.9

All mental health services use data, including the primary outcome, and secondary and health economic outcomes as listed above are extracted from the site (Mental Health NHS Trust) electronic patient record (EPR) by site information management staff using a pro forma and indicating participants by each site's EPR number for each participant. Data collected at T0 are for the period of 12 months preceding the index admission. Data collected at T2 are for the 12 months post discharge from the index admission.

Online survey data on participant contact and non-contact activities are collected using Limesurvey software. Participant contact activity surveys are completed weekly by all peer workers for the duration of delivery of the intervention. Non-contact activity surveys are completed by peer workers and PWCs for 6 randomly selected weeks during the course of delivery of the intervention. Links to the survey are emailed directly to peer workers and PWCs.

All other data are collected by researchers through face-to-face interviews with participants. At T0, once the participant has been entered into the trial and before randomization, the researcher will, in an appropriate location on the inpatient ward where the participant was recruited, complete the baseline (T0) assessment booklet with the participant comprising measures as listed above.

At T1 (end of intervention) – no sooner than 4 months (120 days) post discharge from the index admission and no later than 6 months (180 days) post discharge from the index admission – the researcher will, in an appropriate location in the community (or on an inpatient unit if the participant has been readmitted at that point), complete the end-of-intervention assessment booklet with the participant, comprising measures as listed above. Participants will be asked, at recruitment, to provide their preferred contact details. Where a participant is not contactable, the participant's clinical team will be asked to contact the participant on the study team's behalf. Researchers will make a maximum of 5 attempts to contact each participant.

Recruitment, randomization, allocation, and assessment procedures are indicated in Figure 1.

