### Blinding

2.13

All trial personnel are blind to allocation of participants, with the exception of designated team members involved in communicating allocation to participants (as described above). These team members are not involved in assessment or analysis of trial data. As noted above, all collection of secondary and process outcome data by face-to-face interviews at T0 precedes allocation. All trial and site personnel involved in collection of electronic patient record data, including primary outcome data, are blind to allocation of participants. All trial personnel involved in collection of secondary and process outcome data by face-to-face interview at T1 (end of intervention) are blind to allocation of participants. The following measures are designed to ensure blinding of data collection at T1 is as robust as possible:

1.Participants are asked at the beginning of the interview not to reveal their allocation to the researcher;2.Participants self-complete paper copies of the Manchester Short Assessment of Quality of Life^[46]^ and Herth Hope Index^[48]^ at the beginning of the interview and place these into an envelope unseen by the researcher prior to sealing the envelope. The participant's Study Identification Number is indicated on the paper copies of measures and the outside of the envelope. This is to ensure that a minimum amount of data is collected with the study team blind to allocation should the participant reveal their allocation during the interview;3.If the researcher becomes unblinded, or suspects that they have become unblinded during the course of the interview, at the end of the interview the researcher completes a Blinding of Interview Form, which indicates:a.Whether allocation was revealed by the participant and the number of the question in the interview at which allocation was revealed, orb.Whether the researcher suspected that they had become unblinded during the interview and the number of question in the interview at which allocation might have been revealed, andc.If so, to which group of the trial the researcher thinks the participant had been allocated.

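### Researchers declared blind at T1 are to collect a rating of the peer worker, whom only the intervention arm has, so blinding cannot hold from that item onward

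*Protocol article*

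**What the plan says.** Four parts of the protocol article bear on this.

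- **Blinding (2.13):** "All trial personnel involved in collection of secondary and process outcome data by face-to-face interview at T1 (end of intervention) are blind to allocation". The claim covers process data as well as secondary outcomes.
- **Process measures (2.8.4):** the therapeutic relationship is rated at T1 in two parts. One concerns the mental health professional whom the participant sees most. The other is the participant's rating "about the peer worker, using the STAR Patient version", paired with the peer worker's own rating of that participant on the clinician version.
- **Data collection methods (2.9):** after setting aside patient-record data and the online activity surveys, the article says "All other data are collected by researchers through face-to-face interviews with participants". At T1 the researcher is to "complete the end-of-intervention assessment booklet with the participant, comprising measures as listed above". No measure is exempted.
- **Aim (2.1), repeated under Control (2.7):** "Participants in the control group receive CAU and the Discharge Information Pack". Controls are given no peer worker.

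Section 2.13 lists three safeguards for T1. Participants are asked at the start not to disclose their group. Two scales are sealed before the interview proper: "Participants self-complete paper copies of the Manchester Short Assessment of Quality of Life" and of the Herth Hope Index, placed in an envelope unseen by the researcher. A Blinding of Interview Form records whether allocation was revealed or suspected, and at which question.

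**The concern.** An interviewer who reaches a questionnaire about the participant's peer worker, and either works through it or passes over it, learns the allocation from the instrument itself. Asking participants to stay silent cannot help when the booklet puts the question.

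What is at stake is the set of T1 outcomes taken in the interview outside the envelope, above all the Brief Psychiatric Rating Scale. Participants know their group, so the assessor's ignorance is the main guard against detection bias in these measures. The Introduction names unblinded assessment as a weakness of earlier peer-support trials, and the Discussion offers assessor blinding as part of the remedy. A blinding claim that the trial's own booklet contradicts would weaken that argument.

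**Working it through.** No arithmetic applies. The check is whether sections 2.8.4, 2.9 and 2.13 can all be followed together.

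1. **Is the item specific to one arm?** Section 2.8.4 separates the mental health professional from the peer worker, and the peer worker rates the same participant in return. This is therefore the trial peer worker. Controls have none (2.1, 2.7). That only the intervention arm can answer is an inference, but a firm one. A completed rating points to the intervention arm. A skipped one points to control, except for an intervention participant who never met a peer worker.

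2. **Does the blind researcher collect it?** The rating is participant data at T1. It is neither patient-record data nor an online activity survey, so section 2.9 assigns it to the researcher's face-to-face interview and booklet.

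3. **Is that researcher declared blind for it?** Yes. Section 2.13 names process data explicitly.

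4. **Does any safeguard stop the item from revealing allocation?**

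| Safeguard in 2.13 | What it covers | Effect on this item |
|---|---|---|
| Request not to disclose | Whole interview | None, because the booklet itself asks |
| Sealed envelope | Quality-of-life and hope scales | None, because the peer-worker rating is not in it |
| Blinding of Interview Form | Whole interview | Records unblinding, does not prevent it |

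5. **Which outcomes are exposed?** Those taken in the T1 interview outside the envelope: the Brief Psychiatric Rating Scale, the Social Contacts Assessment, the friendship question added for the Social Outcomes Index, EQ5D-5L, the service-use schedule, and the remaining process measures. Each is exposed only if it is rated or finalised after the peer-worker item. The article does not give the order of the booklet, and Figure 1 is not available here.

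6. **Which are not exposed by this route?** The primary outcome, the other readmission outcomes, bed days, emergency liaison contacts and crisis-team contacts all come from the electronic patient record. The two sealed scales are completed before the item can be reached. The questions on other peer support are asked in both arms at T0 and T1, so they do not reveal allocation by design.

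Steps 1 to 4 give a conflict on the page. Steps 5 and 6 bound its consequences.

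**The case against.** The strongest reply is that the sentence assigning all remaining data to interviews is a summary and cannot be literal. The clinician version of STAR is filled in by the peer worker, and serious adverse events arrive on their own form from the site. An article condenses its protocol, and the full document or the booklet may give the peer-worker rating another route or place it last. This stands as a reason for caution about what happens in practice. It does not remove the conflict: the two counter-examples are not participant interviews, whereas the participant's rating is exactly the kind of data the sentence describes. The article also extends its blinding claim to process data rather than staying silent.

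A reader might infer several stronger things that the document does not support.

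- **That the symptom scale has no protection.** The non-disclosure request and the form both cover it. What it lacks is the sealed envelope and any stated rule that it comes before the revealing item.
- **That symptom ratings are in fact made unblinded.** If the scale precedes the peer-worker item, it can be rated blind as far as this item is concerned. The article also does not say that the scale is observer-rated. It only leaves it out of the self-completed set.
- **That a false-positive rate can be quoted.** Assume 200 interviews per arm and no clustering: the standard error of a standardised difference is √(2/200) = 0.10. An assumed expectation shift of 0.1 SD then gives a two-sided rejection rate of about 17%, and 0.2 SD about 52%. Neither the interview count nor the shifts stand in the document, so these figures only restate the assumptions.

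The article also promises blinding only as far as practicable, and the envelope exists because disclosure during the interview was foreseen. That is fair, but it concerns what a participant might let slip, not a question built into the booklet.

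**Conclusion.** Sections 2.8.4, 2.9 and 2.13 cannot all hold as written. From the peer-worker rating onward, the stated blinding of the T1 interviewer fails, and none of the listed safeguards prevents this.

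The consequence is a risk of detection bias in interviewer-collected T1 outcomes, conditional on their being rated or finalised after that item. Its size cannot be derived from the document. The conclusion rests on two inferences: that the peer worker being rated is the trial's own, and that section 2.9 means what it says about participant data. The primary comparison is not affected by this route, so this is a correction to make rather than a threat to the trial's main result.

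**What to change.** **Remaining T1 interviews.** Complete and lock the symptom scale and the other interviewer-collected outcomes first. Then have the participant self-complete the peer-worker rating and seal it unseen by the researcher, with a same-length page for controls. The simplest form is one identical pack for everyone, holding both pages, of which the participant fills in the one that applies. The researcher then needs no knowledge of the group to hand it over.

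Do not give the task to the unblinded allocation staff, because section 2.13 keeps them out of assessment. Do not give it to the peer worker coordinator either. Coordinators supervise and may line-manage the peer workers, and participants may soften a rating given to them.

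**Interviews already done.** Use the booklet order and the form's question numbers in a sensitivity analysis of interviewer-collected outcomes, limited to ratings made before unblinding. If the order shows that the symptom scale came first, report that, since it answers the concern for that scale. Unblinding may differ by arm, so the restricted comparison is supportive only.

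**Text.** Reword section 2.13 to say how and when the peer-worker rating is collected, and limit the blinding claim to match.

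**Cost.** A minor booklet change, a short amendment and one extra sensitivity analysis, with no extra staff. Few interviews may be left to change. Recruitment closed on March 8, 2019. If the last participant was discharged within a month, around April 8, the 180-day limit for T1 falls around October 5, 2019, or later where discharge was delayed. The article says only that follow-up was still open at submission.

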### Data collection methods

2.9

All mental health services use data, including the primary outcome, and secondary and health economic outcomes as listed above are extracted from the site (Mental Health NHS Trust) electronic patient record (EPR) by site information management staff using a pro forma and indicating participants by each site's EPR number for each participant. Data collected at T0 are for the period of 12 months preceding the index admission. Data collected at T2 are for the 12 months post discharge from the index admission.

Online survey data on participant contact and non-contact activities are collected using Limesurvey software. Participant contact activity surveys are completed weekly by all peer workers for the duration of delivery of the intervention. Non-contact activity surveys are completed by peer workers and PWCs for 6 randomly selected weeks during the course of delivery of the intervention. Links to the survey are emailed directly to peer workers and PWCs.

All other data are collected by researchers through face-to-face interviews with participants. At T0, once the participant has been entered into the trial and before randomization, the researcher will, in an appropriate location on the inpatient ward where the participant was recruited, complete the baseline (T0) assessment booklet with the participant comprising measures as listed above.

At T1 (end of intervention) – no sooner than 4 months (120 days) post discharge from the index admission and no later than 6 months (180 days) post discharge from the index admission – the researcher will, in an appropriate location in the community (or on an inpatient unit if the participant has been readmitted at that point), complete the end-of-intervention assessment booklet with the participant, comprising measures as listed above. Participants will be asked, at recruitment, to provide their preferred contact details. Where a participant is not contactable, the participant's clinical team will be asked to contact the participant on the study team's behalf. Researchers will make a maximum of 5 attempts to contact each participant.

Recruitment, randomization, allocation, and assessment procedures are indicated in Figure 1.

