### Participants

2.4

Participants in the trial are all inpatients in adult acute psychiatric wards who give written consent to participate in the study. Specific inclusion criteria are as follows:

Inpatients of adult acute psychiatric wards (acute admission wards and their equivalents as termed locally) with at least 1 previous psychiatric admission in the preceding 2 years;Aged 18 years or older;Assessed by ward clinical team as likely to be discharged within the next month;Capacity to give informed consent to participate in the research.

Exclusion criteria are as follows:

Having a diagnosis (as recorded in clinical notes) of any organic mental health condition;Having a primary diagnosis (as recorded in clinical notes) of eating disorders, learning disability, or drug or alcohol dependency;Assessed by ward clinical team as unlikely to be discharged within the next month;Assessed by ward clinical team as presenting a current, substantial risk to peer worker.

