Trial participants randomized to peer support are assigned a peer worker by the PWC who introduces the participant to the peer worker, as soon as possible after allocation and prior to discharge. Peer workers are matched to the participant by gender where this is specifically requested by the participant or where this is felt to be appropriate by the clinical team; otherwise no additional matching is undertaken. Participants have at least one meeting with the peer worker prior to discharge, and continue to meet weekly until discharge if discharge is delayed (where this delay exceeds a month, contact drops to a brief fortnightly meeting until discharge). Once discharged, participants have a weekly meeting with the peer worker for 10 weeks, stepping down to 3 further fortnightly meetings (i.e., 13 meetings over a 4-month period post discharge). Meetings are flexible in length, as agreed by participant and peer worker. Peer workers have sufficient time in their work plans to spend half a day per contact, including traveling to and from the meeting, although it is expected that meetings typically range from 60 to 90 minutes. Face-to-face meetings can be supplemented by phone calls, using phones provided by the employer, within the peer worker's working hours.

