Informed by the domains of the Peer Support Principles Framework,^[44]^ in initial meetings peer workers focus on making a connection with participants and on building the relationship. As part of the training, peer workers are equipped with a range of skills and tools with an individual strengths-based focus, and around mapping and appraising community-based resources and social supports. In subsequent meetings, peer workers and participants agree between them which approaches and tools they will use and are free to identify other tools or develop their own. Once in the community, peer workers do not meet participants in their own homes; the focus is on being alongside the participant as they engage, or re-engage, with a range of social spaces and activities in the community. Peer workers use their experiences of mental distress and of using mental health services as a point of connection with the participant, and to validate and encourage the participant to reflect on their own experiences. Peer workers are encouraged, through training and supervision, to listen to and learn from the participant's experiences as part of a reciprocal relationship, especially with respect to understanding each other's diverse experiences of mental health, in relation to culture, gender, sexuality, and so on, as appropriate. There is an emphasis on the peer worker enabling the participant to access social supports, rather than on the peer worker providing support (as a support worker, for example), in order that dependency in the relationship is minimized, with the ending of the peer support discussed at regular intervals. Peer workers are able to attend discharge meetings, case reviews, and care planning meetings, or to attend appointments with mental health professionals with the participant, at the participant's request.

The handbook specifies the support to be received by peer workers. This focuses on the regular group supervision provided by the PWC – with a focus on using personal experiences of mental distress in the peer worker role – with additional individual supervision as necessary. Peer workers constitute their own team and can be line managed by the PWC, or by another mental health worker (where the PWC lacks sufficient experience to manage a team). The peer worker team is enabled to meet together as agreed to provide each other with peer support. The PWC should receive appropriate supervision and support to fulfil their role.

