### Health economic analyses

2.16

The primary economic analysis will take the NHS/Personal Social Services perspective preferred by the National Institute for Health and Clinical Excellence.^[58]^ It will focus on evaluating the net impact of the provision of peer support on resource use over a 12-month period of follow-up, accounting for the cost of contacts with community-based mental health services and any readmission to hospital. A secondary economic analysis will be undertaken using resource utilization and quality-of-life data collected at 4 months post discharge from hospital. This will evaluate the short-term “societal” cost consequences of providing peer support on service use within and outside of the mental health sector (e.g., contact with the police) alongside the extent of any short-term gains in quality-of-life adjusted time spent living in the community (QALYs).

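### Index-admission bed-days between randomisation and discharge fall in neither data window, so days in hospital and, as described, the primary economic analysis omit inpatient use that the intervention could change

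*Protocol article*

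**What the plan says.** All points are from the protocol article.

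- **Record windows** (Data collection methods). For T0: "Data collected at T0 are for the period of 12 months preceding the index admission". For T2: "Data collected at T2 are for the 12 months post discharge from the index admission".
- **Where randomisation falls** (Data collection methods; Recruitment). Baseline is completed during the index stay, and allocation follows it: "At T0, once the participant has been entered into the trial and before randomization, the researcher will, in an appropriate location on the inpatient ward".
- **Time to discharge** (Participants). An inclusion criterion is "Assessed by ward clinical team as likely to be discharged within the next month". The Intervention section also provides for delays of more than a month, with contact then becoming fortnightly.
- **Support before discharge** (Intervention). "Participants have at least one meeting with the peer worker prior to discharge, and continue to meet weekly until discharge if discharge is delayed". Also: "Peer workers are able to attend discharge meetings, case reviews, and care planning meetings", which the same sentence makes subject to the participant's request.
- **Hospital days** (Secondary outcomes). "Days in hospital (for all psychiatric admissions). (T0, T2").
- **Primary economic analysis** (Health economic analyses). Net effect on resource use over 12 months of follow-up, "accounting for the cost of contacts with community-based mental health services and any readmission to hospital".
- **Peer-worker input** (Data collection methods). Contact surveys are completed every week for as long as the intervention is delivered.

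**The concern.** A comparison of resource use between randomised groups should count use from randomisation onward. Here one stretch of post-randomisation inpatient time is not counted, and it is time in which one arm is already receiving the intervention.

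If peer support brought discharge forward or put it back, the change in bed-days would appear neither in the days-in-hospital comparison nor in the inpatient cost as described. The costing would also be lopsided: in-hospital peer-worker time can enter as a cost, while its effect on the index stay, in either direction, cannot enter at all. Any trade-off between a shorter or longer index stay and later readmission would be invisible in an analysis meant to show net impact. An analysis plan written later can repair this only if the missing days are extracted or derived.

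**Working it through.** **1. One timeline.** Let A be the index admission date, R randomisation and D discharge, with A < R < D.

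- T0 window = [A − 12 months, A]
- T2 window = [D, D + 12 months]
- Left out = [A, D] = [A, R] + [R, D]

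The part [A, R] precedes randomisation, so it can differ between arms only by chance. The part [R, D], of length L = D − R, follows randomisation and lies wholly in the gap.

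**2. Does another section close the gap?**

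| Item | Covers [R, D]? |
|---|---|
| Days in hospital | No. It refers to all psychiatric admissions but is tagged T0 and T2, so it takes those windows |
| Primary economic analysis | Not as described. Readmission is the only inpatient item named |
| Peer-worker contact surveys | Yes. They run for the whole delivery period, which includes in-hospital meetings |

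The last two rows together give the asymmetry in the costing.

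**3. Scale of the uncounted time.** The article gives no mean L, so L is assumed. Total days = 590 × L. Share of the time from randomisation to end of follow-up = L / (L + 365).

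| Assumed mean L (days) | 590 × L | L / (L + 365) |
|---|---|---|
| 7 | 4,130 | 1.9% |
| 14 | 8,260 | 3.7% |
| 30 | 17,700 | 7.6% |
| 60 | 35,400 | 14.1% |

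**4. Scale of an arm difference.** Bias arises only if L differs between arms. The article gives no expected difference. An assumed change of 1, 3 or 5 days per intervention participant, with 290 in that arm, is 290 × 1 = 290, 290 × 3 = 870 or 290 × 5 = 1,450 bed-days. None of these would be counted, and the sign could be either.

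**5. The sample size is not affected.** Inputs from the Sample size section: 34% v 22%, 80% power, 5% (two-sided), ICC 0.05 and cluster size 10 in one arm. The design effect is 1 + 9 × 0.05 = 1.45. Per arm, with the pooled-variance formula:

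n = [1.96 × √(0.28 × 0.72 × 2.45) + 0.842 × √(0.34 × 0.66 + 1.45 × 0.22 × 0.78)]² / 0.12² = 265.8

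This rounds to 266 per arm, 532 in total (530 stated). Then 530 / 0.9 = 589 (590 stated). The plan's figures reproduce, and nothing here depends on them.

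**6. Can a fixed window be built?** Because R < D, R + 12 months comes before D + 12 months. For anyone discharged within that period, the 12 months from randomisation are covered by [R, D] plus part of T2. Total bed-days = L + readmission days between D and R + 12 months. Someone still in hospital at R + 12 months contributes the full 12 months. The only new inpatient quantity is L.

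**The case against.** **The discharge-anchored clock is deliberate.** The aim is readmission in the 12 months after discharge, for an intervention that supports discharge. This stands. A reader might infer that the primary outcome is flawed because its time zero follows randomisation. The article does not support that: the primary outcome follows from the stated aim, and the point here is confined to bed-days and cost.

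**The route to an effect is thin.** Attendance at discharge meetings is only at the participant's request, the guaranteed pre-discharge dose is one meeting, likely discharge is judged by the ward team at eligibility, and most of the work described takes place in the community. This also stands, to the extent that the article neither claims nor shows an effect on discharge timing. It does not rule one out, and without counting these days the trial would not know.

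**The economics section is a condensed paragraph.** It does not say that only community contacts and readmissions count, it gives no start date for its 12 months, and a fuller health-economics plan may exist. That is why the claim about cost is limited to the analysis as described. It does not rescue the hospital-days outcome, whose windows are stated outright.

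**A percentage of the planned benefit.** A reader might set an assumed 3-day arm difference against the planned 12-point reduction. With readmissions assumed to last 20 to 60 days, that reduction saves 0.12 × 20 = 2.4 to 0.12 × 60 = 7.2 bed-days per participant, so 3 days would be 42% to 125% of it. This divides one assumption by another. It also allows only one avoided readmission per person, although the outcome counts all admissions. It should not be used as an estimate.

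**Conclusion.** The point holds for the days-in-hospital comparison and, as described, for the primary economic analysis. It rests on the two stated windows and on randomisation taking place before discharge, and neither needs an assumption. The size and direction of any bias are unknown, because the article gives neither the mean interval nor an expected effect on the index stay. If the interval does not differ by arm, there is no bias in the arm comparison. The change is worth making because the omitted time follows randomisation and the repair is cheap.

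Two further readings go beyond the text. A reader might infer that anyone not discharged drops out of the intention-to-treat set. The article does limit that set to participants with a recorded outcome, but it leaves missing-data handling to the analysis plan, excludes people judged unlikely to be discharged within a month, and gives no figure for non-discharge. A reader might also infer that earlier discharge followed by readmission would score purely as harm, or a longer stay purely as benefit. The documents support only the weaker statement that such a trade-off could not be seen.

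**What to change.** - Derive index-admission bed-days from randomisation to discharge. The discharge date already anchors T1 and T2, and the randomisation date should be held by the online randomisation service.
- Report these bed-days by arm.
- Add a supporting analysis of total psychiatric bed-days, and of NHS cost, that includes them. Preferably run both over a fixed period from randomisation (for example 12 months). A window from randomisation to 12 months after discharge would vary in length with the discharge date and give longer index stays more time to accrue days.
- Keep the discharge-anchored primary outcome and the existing post-discharge days outcome as they are.

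**Cost.** One derived variable, some wording in the analysis and health-economics plans, and slightly more analysis. The fixed window needs dated readmissions and contacts, not 12-month totals; the article does not say which the extraction form records. Index days will add some variance to total bed-days. Sample size and participant burden do not change. At submission of the article follow-up was still open, and the analysis plan was to be signed off before unblinding, so the change could be made without knowledge of results.
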